#### Training of the program instructors

We provide training for instructors of both the FEEL and the Functional Training program. These trainings cover overarching aspects such as the program objectives and structure. Additionally, we review the individual course sessions by discussing their topics, main goals, exercise types, and additional content. Finally, we introduce instructors to the program manual and demonstrated selected content through practical examples. For FEEL program instructors, a supplementary workshop focuses on fostering a socially enriched exercise setting (key element 1; see Appendix 3 for further information).

After the initial training, we provide ongoing coaching throughout the program. For the FEEL program, we meet with instructors to discuss every course session in advance. For the Functional Training program, we schedule coaching sessions ahead of the third and sixth-course sessions. Regardless of the program, all instructors can reach out to one of the principal investigators at any time during the course period to ask questions or address issues as part of our troubleshooting support.

### Sample size

We conducted the sample size calculation a priori to the main study using the powerlmm package in R (Version 4.2.2). Based on prior research [14, 20, 87, 88], we assumed an effect size of *d* = 0.5 for differences in PAAR (primary outcome) between the IG and the CG over time (t1, t2, t3), with a statistical power of ≥ 80% and a two-sided significance level of α = 0.05. Additionally, we set the baseline intraclass correlation coefficient (ICC) to ICC = 0.5 and the random slope variance to 0.02. We anticipated a dropout rate of 20% at both after t1 and after t2. Accordingly, the calculation determined a minimum required sample size of N = 160 participants.

### Procedure

We recruit participants separately by study site starting several weeks in advance of the respective course periods (waves). Recruitment takes place within the respective universities, e.g., via university sports, student and occupational health management, student councils, and student organizations, at events (e.g., introductory weeks, Mental Health Days), in specific groups such as the student choir or trainees and at certain central locations (canteen, library). Participants outside the university are recruited via local companies and social media advertising. In all cases, various print (e.g., posters, flyers) and digital media (e.g., mailings, newsletters, websites, digital displays and platforms, posts/reels in social media and chat groups, or on companies'intranet) are used.

The recruitment material includes a link to a website where individuals can find detailed information about the study and data protection (see Appendix 4). The website also mentions that we offer two distinct exercise programs explicitly designed for those returning to or starting exercise. These programs focus on providing exercise tailored to personal needs. After giving their informed consent, individuals can register for the exercise programs (see Fig. 5). They can choose their preferred course time (e.g., course time A or B), provide their contact details, and complete a questionnaire to check the inclusion criteria. Registration is possible until the second-course session.

**Fig. 5 Fig5:**
[figure not shown]
Study flow chart

During the registration phase, we continuously monitor the course enrolment and the inclusion criteria of registered participants. Individuals not meeting the inclusion criteria will be notified by email, and their registration will be canceled. Suppose there is an uneven distribution of registrations among eligible participants. In that case, a blinded project staff member will assess whether participants can switch to another course or if a certain course time should be temporarily withheld from registration.

One week before the course begins, we send the baseline questionnaire (t1) via email, requesting that participants complete it within a week. A reminder is sent three days before the completion deadline. If the questionnaire has not been completed by the deadline, we reach out personally. Within the first week after the course begins, participants who attended the first session but have not completed the questionnaire are contacted again.

One day before the course starts, participants receive a separate e-mail with directions to the course location and the contact details of the course instructor. Additionally, if an individual was absent without notice from the first session, we personally reach out in a friendly manner to inquire about their participation. A blinded staff member is responsible for all communication with the participants. Instructors also contact participants who have missed two consecutive sessions to encourage their continued participation.

After the last course session and 8 weeks after completion, participants receive an e-mail inviting them to complete the post (t_2_) and follow-up (t_3_) questionnaires. The reminder process will correspond with the baseline survey.

Participation in the FEEL and Functional Training program is free of charge. As an incentive, three €50 vouchers are raffled per site and waved among those who complete all three surveys. Instructors are compensated according to current standard rates per course session, which includes time for preparation and training.

Participants who either formally announce their withdrawal from the exercise program or fail to attend without prior notice are classified as dropouts. We record dropout time. Participants can voluntarily provide reasons, which are categorized as follows:Health (e.g., injury, illness)Time (e.g., professional or personal commitments, unable to attend scheduled sessions)Peers (e.g., a colleague was not accepted into the program)Personal reasons (e.g., bereavement)Program not appealing/disappointing; lost interestLanguage barriers (e.g., instructor realized during the program that they have limited German proficiency)No show/no reason provided

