## Methods

### Design

The FEEL study is a cluster randomized controlled trial with an IG (exercise program: FEEL) and active CG (exercise program: Functional Training) with three points of assessment (t1: pre, t2: post, t3: follow-up). We designed the study to investigate the superiority of the intervention condition to the control condition from an efficacy perspective [77]. Participants are allocated to each condition in a 1:1 ratio. The FEEL and Functional Training programs are both carried out in courses over eight consecutive weeks with one 90-min session per week in groups of approximately 12–15 people but have different thematic and methodological focuses. As the FEEL study is a cooperation project between the University of Bern, Switzerland, and the University of Tübingen, Germany, the multicenter study is conducted at these two sites from September 2024 to August 2025 in at least three study waves, with a total of 160 participants. We registered the trial on https://drks.de with ID number DRKS00035302 and received approval from the local ethics committees at the University of Tübingen, Germany (ID: A2.5.4–334.1_hb) and the University of Bern, Switzerland (ID: 2024–02-06). With the present study protocol, we adhere to the Standard Protocol Items: Recommendations for Intervention Trials (SPIRIT) guidelines [78] and aligned it with the Template for Intervention Description and Replication (TIDieR) Checklist and Guide [79].

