### Randomization

Cluster randomization occurs four weeks before the course begins (see Fig. 5) for practical reasons: the FEEL and Functional Training programs require indoor spaces in municipal or university halls, which are in high demand. The courses are scheduled at fixed times during each wave, and instructors must be available at these times.

The cluster randomization is conducted separately for the two study sites. This stratification ensures that the courses within each study site are evenly distributed between IG and CG. The assignment of course time A and course time B to either the intervention or control condition is determined by a computerized random number generator (random.org) operated by a researcher not involved in the project. We apply an equal allocation ratio of 1:1, meaning there is a 50% probability that either course time A or B will be assigned to the intervention, with the other time allocated to the control condition.

Table 2 shows the planned allocation of the study groups. We expect an average group size of 12 participants. This leads to a slightly larger total sample size than the required *N* = 160 participants (see section on sample size above).

**Table 2 Tab2:** Planned allocation of the study groups

	Total	Wave 1						Wave 2				Wave 3			
Course clusters	7	A1		B1		B2		A2		B3		A3		B4	
Course allocations (ratio: 1:1)	14	IG	CG	IG	CG	IG	CG	IG	CG	IG	CG	IG	CG	IG	CG
Expected n		12	12	12	12	12	12	12	12	12	12	12	12	12	12
Sum n	168	24		24		24		24		24		24		24	

A = study site A, B = study site B, *IG* intervention group, *CG* control group

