### Blinding

The course participants are blinded to the specific nature of the intervention. During recruitment, the course descriptions are limited to elements common to both courses (see section on procedure above). Participants are informed that two distinct courses are being conducted to study their effects on health, well-being, and exercise behaviors. In all communication, both programs are referred to as the"FEEL"program.

The course instructors are not blinded due to the apparent differences between the two programs and the association of the FEEL instructors with the project. Similarly, the principal investigators and project staff are not blinded, except for the staff member responsible for participant communication during the registration and survey process. Additionally, the statistician is blinded.

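### Some t1 baseline forms can be completed after session 1, and registration until session 2 conflicts with the screening window in Table 3

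*Protocol article*

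**What the plan says.** The Procedure section gives the normal route for t1: "One week before the course begins, we send the baseline questionnaire (t1) via email, requesting that participants complete it within a week". A reminder goes out three days before the deadline, and people who miss the deadline are approached personally. A last step follows in the first week of the course, when "participants who attended the first session but have not completed the questionnaire are contacted again".

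On enrolment, the same section states: "Registration is possible until the second-course session". Registrants pick their preferred course time, and course time is the unit that is randomised. The Randomization section fixes the order of events: "Cluster randomization occurs four weeks before the course begins".

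Table 3 places screening (t0) at weeks -4 to -1 and t1 at week 0, and the Design section labels t1 as the pre assessment. Under Statistical analysis, each outcome is modelled on group, time (t1, t2, t3) and their interaction. The modified intention-to-treat set leaves out only people who never attended a session.

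**The concern.** There are two separate issues.

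The first is the meaning of baseline. A t1 form obtained through the last contact is completed after the participant has been exposed. Those participants attended a session, so they stay in the modified intention-to-treat set, and the article states no rule that separates their t1 from an unexposed one. By Table 1, session 1 is group-building in the FEEL arm and the basics of Functional Training in the control arm. A shift in self-rated affect regulation (PAAR) after that session need not be equal in the two arms, and any difference enters the primary contrast through t1.

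The second is entry after allocation. Someone who registers between sessions 1 and 2 chooses between courses that are already allocated and already running. That person cannot have been screened in weeks -4 to -1. Once a session has been held there are attendees who could describe it, so some room for selection into an arm exists if content spreads by word of mouth.

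**Working it through.** **Order of events, from the stated times**

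| Time | Event | Source |
|---|---|---|
| Week -4 | Course times randomised | Randomization |
| Weeks -4 to -1 | Screening, t0 | Table 3 |
| Week -1 | t1 sent, due within a week | Procedure |
| Week 0 | Session 1; nominal t1 | Procedure, Table 3 |
| Weeks 0 to 1 | t1 sought again from session-1 attenders without a form | Procedure |
| About week 1 | Session 2; registration closes | Procedure |

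The programmes are "both carried out in courses over eight consecutive weeks with one 90-min session per week", so a late t1 from a session-1 attender follows 1 of 8 sessions, or 12.5% of the programme.

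**Who is affected**

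- Session-1 attenders reached by the last contact: t1 is post-exposure.
- Registrants after session 1 who did not attend it: t1 is late by calendar but unexposed, provided it is completed before their own first session. For them the issues are the Table 3 window and choice after allocation.

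**Size of the baseline effect**

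The plan gives no figure to reproduce here. Let f be the share of t1 forms completed after session 1 in each arm, and δ the shift in PAAR that session 1 causes. The contrast in change from baseline is then approximately

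true effect - (f_IG × δ_IG - f_CG × δ_CG).

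If f is the same in both arms and a share s of the final effect d is present after session 1, then δ_IG - δ_CG = s × d, and the contrast becomes d × (1 - f × s). The Sample size section gives d = 0.5. The documents give neither f nor s; the ranges below are assumptions.

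| f | s | f × s | 0.5 × (1 - f × s) |
|---|---|---|---|
| 10% | 1/8 | 1.25% | 0.494 |
| 10% | 1/4 | 2.5% | 0.4875 |
| 30% | 1/8 | 3.75% | 0.481 |
| 30% | 1/4 | 7.5% | 0.4625 |

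The dilution is thus about 1-8%. Taking the plan's N = 160 as the reference, holding power would need 160 / (1 - f × s)²: 160 / 0.9875² gives 165, and 160 / 0.925² gives 187.

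The general formula also shows why the sign is not fixed. If session 1 raises PAAR more in the control arm, or if late forms are commoner there, the contrast can be inflated instead.

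**A secondary outcome**

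The exercise-volume questionnaire (BSA-F) covers the past four weeks. One 90-minute session, if the participant counts it, adds up to 90 / 4 = 22.5 min/week to baseline exercise. This can happen in either arm, so it cancels in the contrast to the extent that late shares are equal.

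**The case against.** The strongest reply is that late collection is a fallback. It comes after an advance mailing, a reminder and a personal contact at the deadline, so it reaches only a remainder. That is right. A reader might infer that baseline is routinely measured after exposure; the Procedure section does not support this.

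A reader might also infer that every late registrant has a post-exposure baseline. That does not follow, because someone who missed session 1 has not been exposed.

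A third tempting inference is that late entrants know what each course contains and that participant blinding is therefore broken. The documents do not show this. The Blinding section states: "During recruitment, the course descriptions are limited to elements common to both courses". Both programmes carry the same name in all communication, and a blinded staff member handles contact with participants. Word of mouth is possible, and these measures do not prevent it, but it remains an inference. Moreover, choosing a course time after randomisation is a feature of the whole design, and an earlier registration deadline would not remove it.

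A large first-session shift is also hard to defend. FEEL session 1 is mainly group-building, and affective responses to exercise are the topic of session 2. A shift of a quarter to a half of d after one session would be a high assumption, so the working uses 1/8 to 1/4.

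Finally, handling of out-of-window forms is often left to an analysis plan, and Table 3 may be a nominal schedule. Both points have some force. But collecting t1 after session 1 is a step the protocol sets out, and following it as written puts some exposed values into the pre level of the primary contrast.

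**Conclusion.** The point holds in a limited form. A subset of t1 values in the primary contrast can follow one of eight sessions, and registration until session 2 does not fit the t0 window in Table 3. Under the assumed ranges (10-30% late forms, 1/8 to 1/4 of the effect present after session 1, equal late shares by arm), d = 0.5 is diluted by about 1-8%. The true size is unknown and probably small. Under these assumptions the bias is towards no difference, but the direction could differ. Selection by late registrants is possible and not demonstrated. This is a cheap improvement and no threat to the trial's validity.

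**What to change.** - Use survey completion dates, if they were retained (the article does not say so), together with the instructors' attendance lists, to flag each t1 completed after the participant's first attended session.
- In the primary analysis, treat flagged t1 values as missing under the multiple imputation already planned. A constrained longitudinal model is an alternative, but it assumes equal baseline means in the two arms, which enrolment after allocation could weaken. Keep the flagged values in a sensitivity analysis.
- Add a sensitivity analysis without people who registered after session 1.
- Report both counts by arm: late t1 forms and post-session-1 registrants.
- Reconcile the registration and t1 procedures with the t0 and t1 timing in Table 3.
- Close registration before session 1 only if a wave remains. The Trial status section puts the last randomisation at the end of summer 2025 and the article appeared on 28 November 2025, so this is probably no longer possible.

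The cost is the loss of some t1 values, probably few, and a slight fall in precision. No new data collection is needed if completion dates exist.

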### Randomization

Cluster randomization occurs four weeks before the course begins (see Fig. 5) for practical reasons: the FEEL and Functional Training programs require indoor spaces in municipal or university halls, which are in high demand. The courses are scheduled at fixed times during each wave, and instructors must be available at these times.

The cluster randomization is conducted separately for the two study sites. This stratification ensures that the courses within each study site are evenly distributed between IG and CG. The assignment of course time A and course time B to either the intervention or control condition is determined by a computerized random number generator (random.org) operated by a researcher not involved in the project. We apply an equal allocation ratio of 1:1, meaning there is a 50% probability that either course time A or B will be assigned to the intervention, with the other time allocated to the control condition.

Table 2 shows the planned allocation of the study groups. We expect an average group size of 12 participants. This leads to a slightly larger total sample size than the required *N* = 160 participants (see section on sample size above).

**Table 2 Tab2:** Planned allocation of the study groups

	Total	Wave 1						Wave 2				Wave 3			
Course clusters	7	A1		B1		B2		A2		B3		A3		B4	
Course allocations (ratio: 1:1)	14	IG	CG	IG	CG	IG	CG	IG	CG	IG	CG	IG	CG	IG	CG
Expected n		12	12	12	12	12	12	12	12	12	12	12	12	12	12
Sum n	168	24		24		24		24		24		24		24	

A = study site A, B = study site B, *IG* intervention group, *CG* control group

### Blinding

The course participants are blinded to the specific nature of the intervention. During recruitment, the course descriptions are limited to elements common to both courses (see section on procedure above). Participants are informed that two distinct courses are being conducted to study their effects on health, well-being, and exercise behaviors. In all communication, both programs are referred to as the"FEEL"program.

The course instructors are not blinded due to the apparent differences between the two programs and the association of the FEEL instructors with the project. Similarly, the principal investigators and project staff are not blinded, except for the staff member responsible for participant communication during the registration and survey process. Additionally, the statistician is blinded.

### Data collection methods

#### Primary outcome

##### Physical activity-Related Affect Regulation (PAAR)

PAAR is assessed using a scale developed by Sudeck and Pfeifer ([13], see Table 3). Originally comprising four items, the scale primarily measured the competence to use PA to reduce negative affective states (e.g.,"If my mood is unpleasant, I am able to improve it through exercise"or"I can relieve built-up stress or inner tension with exercise"). Participants rate their agreement with each statement on a 5-point Likert scale ranging from 1 (strongly disagree) to 5 (strongly agree). To broaden the scale’s scope and include the competence to enhance positive affective states through PA, two additional items were incorporated: “I am able to feel revitalized or energized through PA” and “I can use exercise to relax.” These two items were formulated based on the German version of the subjective Vitality Scales [98]. In a preliminary study with 456 participants, the revised scale of PA-related affect regulation demonstrated strong factor loadings (see Appendix 5) and good internal consistency (α = 0.941). We will use the sum of the six items for further analyses.

**Table 3 Tab3:** Assessments of the FEEL study

**Characteristics**		**Questionnaires**	**Timepoint**			
			**t0**	**t1**	**t2**	**t3**
			**-4 to -1 weeks**	**0 week**	**8 weeks**	**16 weeks**
***Screening and Study Inclusion***						
Diagnosed mental illness	List of diseases based on Federal Statistical Office health report [76]		x			
Demographics	Age, gender		x			
Volume of exercise	BSA-F [81]		x	x	x	x
***Primary outcome***						
PA-Related Affect Regulation		Subscale from the PAHCO-questionnaire [13]		x	x	x
***Secondary outcomes***						
Affective exercise experiences		AFFEXX [9]; German version [89]		x	x	x
Motivational competence		Questionnaire to assess motivational competence [90]		x	x	
Exercise behavior		Exercise activities in the last four weeks; BSA-F [81]	x	x	x	x
		Habitual leisure-time PA; EHIS-PAQ [91]		x	x	x
Affective well-being		WHO-5 Well-being Index ; German version [92]		x	x	x
***Potential confounding variables and control variables***						
Body-Mass-Index		Self-reported height and weight		x		
Education level		List of highest formal education		x		
Participants sympathy and perceived competence of instructors		Subscale from LMX-MDM [93]			x	
		Questionnaire to assess instructor’s motivational, adaptive, and organizational competencies [94]			x	
Perceived fitness		Subscale from PEPS [95]		x	x	x
Movement competence		Subscales from the PAHCO-questionnaire [13]		x	x	x
Control competence for physical training				x	x	x
PA-specific self-control				x	x	x
***Implementation outcomes***						
Satisfaction with the programs		Single-item question [66]				
Acceptability of the programs		AIM [96]			x	
Appropriateness of the programs		IAM [96]			x	
Feasibility of the programs		FIM [96]			x	
Treatment fidelity		Standardized notation sheets for each session			x	
Attendance rate and reasons for absences		Absence list and open-ended question			x	
Suggestions for improving the programs		Open-ended question			x	
Delivered contents and learning experiences in the exercise programs		based on research of Grüne [97]			x	
Experiences with (re-)entering exercise in the programs		Semi-structured interview				x

*Note. PA* = Physical activity

